#### Primary outcome

The primary outcome of self-perceived limitation of shoulder, arm and hand function will be assessed with the first module of the DASH [16], which is considered a valid and reliable test in clinical practice [17]. Using a total of 30 questions, we will assess the restriction relating to the function and activity of the shoulder, arm and hand in daily living, as well as self-esteem and potentially existing symptoms of the shoulder, arm and hand, such as pain or prickle. The endpoint will be a score calculated from the ratings of the individual responses (1 is the best value, 5 the worst).

#### Secondary outcome

For objective proof of a functional improvement between the beginning and the end of the intervention, the Wolf Motor Function Test–Orthopaedic version (WMFT-O) [18] was conducted. The WMFT-O is an adapted version of the basic WMFT [19] with good inter- and intra-rater reliability. The WMFT-O includes 20 arm motion tasks of daily living that will be examined and evaluated in terms of time, functional capacity and quality of movement, arranged hierarchically and increasing from coarse movements in the elbow and shoulder area to more complex and dexterous tasks in the fingers and the hand area.

### Intervention

Both the intervention group and the control group received physical and occupational therapy for a period of 3 weeks; concomitant interventions were not restricted. The additional robot-assisted therapy commenced as early as 4 weeks after surgery and not later than 7 weeks after surgery. There are no evidence-based guidelines or requirements on the content, duration or intensity of rehabilitation after shoulder injuries. Typically the therapeutic content consists of exercises for stabilisation and mobilisation of the shoulder and the surrounding joints, as well as muscle strengthening (three to six times per week for 25–30 minutes). The obtained conventional physical and occupational therapy will be documented but not influenced. The frequency and duration of individual training schedules, as well as adverse events, will be recorded in a protocol. Serious adverse events will be treated as criteria for discontinuing the interventions.

The intervention group received robot-assisted training in addition to the protocol intervention. The robot-assisted training will be performed using the clinically evaluated Armeo®Spring medical device. By means of sensory orthosis, arm movements will be supported and transmitted to a computer system and visually shown on a screen. Furthermore, audio feedback elements and augmented performance feedback will be used for guidance. The Armeo®Spring device encourages patients with motivating game-like exercises in an inspiring virtual environment. The sensor-based computer system calculates game kinetics for 3D animation of arm functions, including grasping and goal-orientated functional reaching, as well as object manipulation (e.g., throwing a Frisbee). The mechanism to support the weight of the arm will be increased or decreased gradually to adapt to the ability of the user. Thus, the participant will have the ability to perform targeted and controlled movements in accordance with medical safety standards, including the movement limit as suggested by the operating physician.

Preceding every therapy unit, saddle height and joint positioning of the functional segment parts of the exoskeleton will be individually adjusted to the upper extremity proportion of the affected arm of the participant. With the participant in an upright seating position with the spine on the back rest, the participant’s arm will be attached to the exoskeleton with Velcro belts. A calibration of the ROM using the orthosis will be performed by the participants and assessed to calculate an individual game-specific motion envelope. This calibration will help to configure a safe environment for shoulder movements of the participants and will prevent overload and excessive demands. All participants of the intervention group at all three sites (*n* = 30) will receive a 3-week robotic intervention in a standardised training setting with supervised exercise four times per week for 30 minutes per session.

The normative levels of exercise capacity are inspired by a previous pilot study [8], and a rough guideline was created in consensus with the three centres. To create this guideline the 17 existing exercises were categorised according to the direction of the movement. Then 12 of the 17 existing exercises were selected for training of patients after PHF on the basis of the categorised movement directions. These 12 exercises are illustrated and described in Fig. 2 and Table 1.

**Fig. 2 Fig2:**
[figure not shown]
**a**–**l** Armeo®Spring games

**Table 1 Tab1:** Description of the 12 exercises

Name of the task	Task description	Functional challenge
A. High flyer	Collect the coins while flying. Avoid obstacles like bombs and birds.	Flex and extend your shoulder to move up and down.
B. Rain mug	Catch the raindrops with your mug.	Abduct and adduct your shoulder horizontally to move the mug to the left and right sides.
C. Brick breaker	Destroy the bricks with the ball by controlling the moving platform. Making sure not to lose the ball.	Abduct and adduct your shoulder horizontally to move to the left and right sides.
D. Frisbee	Target the Frisbee at the balloons and bring the balloons to burst.	Flex, extend, adduct and abduct your shoulder. Bend and straighten your wrist to burst the balloons.
E. Helicopter rescue	Steer helicopters and rescue your robot friends off the roofs of buildings. Hover over them in order to pick them up.	Abduct and adduct your shoulder horizontally to move to the left and right sides. Rotate the forearm inward and outward to open and close the loading door of the helicopter.
F. Balloons	Catch the balloons while avoiding obstacles like bombs and birds.	Flex and extend your shoulder to move up and down. Abduct and adduct your shoulder horizontally to move to the left and right sides.
G. Fishing	Collect the fish and other aquatic animals, but no waste.	Flex and extend your shoulder to move up and down. Abduct and adduct your shoulder horizontally to move to the left and right sides.
H. Treasure Island	Take the key and roll the ball along the path over the bridge up to the treasure chest. Try to collect coins while doing this, and avoid the obstacles.	Flex and extend your shoulder to move up and down. Abduct and adduct your shoulder horizontally to move to the left and right sides.
I. Roll the ball	Move the ball and collect coins, avoiding the obstacles, like bugs and bombs.	Flex, extend, adduct and abduct your shoulder to move the ball.
J. Supermarket	Take the products, which are on the shopping list, from the shelves and put them in the trolley.	Flex, extend, adduct and abduct your shoulder to move the hand with which you can grab the products.
K. Diving	Collect all the coins in the underwater world while avoiding the bombs.	Flex, extend, adduct and abduct your shoulder to move the diver.
L. Farmer	Maintain your garden by using a variety of transaction types, from sowing to harvesting.	Flex, extend, adduct and abduct your shoulder to move the hand with which you can (e.g., watering the seed).

A plan for the 3-week intervention was created in which the exercises gradually increased from 1D up to 3D movements. Each exercise will take 1–3 min, depending on the task and level of difficulty chosen. Each training unit will start with exercise in a pre-defined order, as shown in Fig. 3, whereas progression will depend on the participant’s current physical performance ability, which will be decided by the therapist. Progression within one unit will be achieved by gradually increasing the level of difficulty and the number of repetitions of a single exercise and thus the duration of the exercise within one training unit. Progression of shoulder function over the intervention period will be achieved by gradually increasing dimensionality of the exercise and by performing different exercises, which require the participant to use more joint segments.

**Fig. 3 Fig3:**
[figure not shown]
Training schedule with games and directions of movement

### Statistics

The centre and the number of treatment units will be regarded as possible covariates for the primary outcome. All data assessed will be described descriptively (mean, SD, 95% CI and median for metric variables; frequency and percentile for categorical variables). After checking the data for normal distribution by comparing the distribution histograms and Shapiro-Wilk test, the group comparison will be carried out with the *t* test or the rank-based Wilcoxon test. For the primary outcome analysis of covariance with study centre, number of therapy units (to take account of the training inhomogeneity) and injury severity (to take account of the patient’s homogeneity) as covariates will be performed. The secondary outcome (WMFT) will be analysed to generate study hypotheses using the methods described above. Inferential statistics will follow an intention-to-treat approach with mean imputation or regression imputation for all randomised patients with incomplete datasets if deemed necessary. Per-protocol analysis will be performed for evaluation of the efficacy of the intervention in patients with complete datasets and without protocol violations.

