**Methods/design:**

Patients aged between 35 and 66 years with proximal humeral fracture and surgical treatment will be recruited at three different clinics in Germany and randomised into an intervention group and a control group. Participants will be assessed before randomisation and followed after completing an intervention period of 3 weeks and additionally after 3, 6 and 12 months. The baseline assessment will include cognition (Short Orientation-Memory-Concentration Test); level of pain in the affected arm; ability to work; gait speed (10-m walk); disability of the arm, shoulder and hand (Disabilities of the Arm, Shoulder and Hand Outcome Measure [DASH]); range of motion of the affected arm (goniometer measurement); visual acuity; and motor function of orthopaedic patients (Wolf Motor Function Test–Orthopaedic version [WMFT-O]). Clinical follow-up directly after the intervention will include assessment of disability of the arm, shoulder and hand (DASH) as well as range of motion and motor function (WMFT-O). The primary outcome parameter will be the DASH, and the secondary outcome parameter will be the WMFT-O. The long-term results will be assessed prospectively by postal follow-up. All patients will receive conventional occupational and physical therapy. The intervention group will receive additional robot-assisted training using the Armeo®Spring robot for 3 weeks.

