### Sample size

Adults in the working population aged between 35 and 66 years will be recruited at all three sites. In a pilot study [8], our group was able to measure an improvement in function with the Disabilities of the Arm, Shoulder and Hand Outcome Measure (DASH) score (median 47 [mean 46 ± 20 SD] to median 34 [mean 32 ± 15 SD]). As a result of a power analysis based on these results, 26 patients per group will be required to achieve 80% power at a significance level of α = 0.05. With an expected drop-out rate of 10%, a total of 60 patients should be recruited, comprising 20 patients at each of the 3 sites.

Inclusion criteria for both groups will be surgical treatment of the shoulder joint after upper arm fracture classified as AO Foundation/Association for the Study of Internal Fixation (Arbeitsgemeinschaft Osteosynthese; AO) type 11 [10]. Participants will be included between the fourth and seventh weeks after surgery. The participant population will be stratified by fracture location (subcapital/capital) and handedness.

Exclusion criteria will be determined during baseline assessment. Participants with limited cognition as defined by a score < 10 points on the Short Orientation-Memory-Concentration Test (SOMC), inadequate level of pain during movement of the affected shoulder joint (pain score > 5 on a pain visual analogue scale [VAS]), strongly limited vision or hearing, heart failure (New York Heart Association stage III-IV), chronic obstructive pulmonary disease with Global Initiative for Chronic Obstructive Lung Disease (GOLD) stage III-IV, walking speed < 0.8 m/second, isolated tuberculum majus fracture of the humerus (AO 11, A1), or fractures with involvement of the glenoid cavity, as well as double fractures or injury of the plexus or the axillary nerve, will be excluded. All participants will give their written informed consent to the study administrators at each centre prior to the clinical baseline assessment.

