### Clinical assessment

The estimated total duration of clinical baseline and follow-up assessments will be 160–180 minutes. The clinical assessment will be carried out for all participants before the first potential training session (baseline) and after the last potential training session (follow-up 1 at 3–5 weeks after baseline). For analysis of sustainability, further postal follow-up assessments (2, 3 and 4) will be carried out 3, 6 and 12 months after the baseline assessment (Fig. 1). In these follow-up assessments, only the DASH and the ability to work (what job to what extent) will be evaluated. All assessments will be performed by trained assessors.

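### The primary DASH comparison has two unranked analyses, one picked by a normality test, and no named visit

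*Protocol article*

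**What the plan says.** **Outcome.** The Abstract states: "The primary outcome parameter will be the DASH, and the secondary outcome parameter will be the WMFT-O". The Primary outcome section defines the endpoint as a score built from the item ratings. It names no visit and does not say whether the final value or the change is compared.

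**Visits.** Under Clinical assessment, DASH is taken at baseline and "after the last potential training session (follow-up 1 at 3–5 weeks after baseline"). After that, "further postal follow-up assessments (2, 3 and 4) will be carried out 3, 6 and 12 months after the baseline assessment". The stated purpose of these later visits is to analyse sustainability.

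**Analysis.** The Statistics section says: "After checking the data for normal distribution by comparing the distribution histograms and Shapiro-Wilk test, the group comparison will be carried out with". Two candidates are then named, a t test and a Wilcoxon rank test. The next sentence begins "For the primary outcome analysis of covariance with study centre, number of therapy units" and adds injury severity as a third covariate. The section opens by calling centre and number of treatment units only possible covariates.

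**Sample size.** The article states that "26 patients per group will be required to achieve 80% power". The test level is given as 0.05, without saying whether it is one-sided or two-sided. The calculation is based on a pilot DASH that went from "median 47 [mean 46 ± 20 SD] to median 34 [mean 32 ± 15 SD").

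**The concern.** A confirmatory claim needs one quantity, at one visit, tested one way. Here two p-values are planned for the primary outcome and neither is put first. One of the two is itself chosen after looking at the outcome distribution. The visit is left to inference.

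Two things are at stake. First, if the favourable result of two analyses can be presented as primary, the type I error exceeds the 0.05 on which the sample size rests. Second, the t test estimates a difference in means and the Wilcoxon test compares ranks, so the question answered depends on the sample drawn. Neither problem is a detail that a condensed article merely leaves out: the article commits to the gate and to the second analysis.

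**Working it through.** **1. Which analysis does the stated sample size belong to?**
- Difference: 46 − 32 = 14 points.
- Pooled SD: √((20² + 15²)/2) = √312.5 = 17.68.
- Standardised difference: 14/17.68 = 0.79.
- Normal approximation, two-sided 0.05, 80% power: n = 2(1.960 + 0.842)²/0.792² = 25.03, so 26 per group.
- The exact t calculation gives 26.02 and a power of 79.96% at 26.
- A one-sided test would need only 20 or 21, so the plan is two-sided.
- Drop-out: 52/0.9 = 57.8, so 58, rounded up to 60 (20 per site).

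The stated number is therefore reproduced as **one unadjusted two-sided t test, at one visit, at full alpha**. The sample size points to the unadjusted test, while the ANCOVA sentence points to the adjusted one.

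**2. Type I error under the null.** There were 10,000 simulated trials per row, 26 per arm, with normal outcomes at four equally correlated visits. The gate uses Shapiro-Wilk by arm at 0.05. The ANCOVA uses the covariates that the article lists: centre, therapy units and severity.

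Assumptions not in the documents are the residual between-visit correlation, the share of DASH variance explained by severity, and therapy units being independent of arm. The last one is favourable to the plan. The simulation error is about 0.2 percentage points at 5% and 0.4 at 15%.

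| Correlation | Variance explained by severity | Gated test, one visit | ANCOVA, one visit | Better of the two, one visit | t test, any of 4 visits |
|---|---|---|---|---|---|
| 0.5 | 0 | 5.0% | 4.9% | 6.3% | 15.6% |
| 0.7 | 0 | 5.0% | 4.8% | 6.3% | 13.4% |
| 0.8 | 0 | 4.7% | 4.5% | 6.0% | 11.5% |
| 0.5 | 10% | 4.7% | 5.1% | 6.9% | 14.8% |
| 0.5 | 30% | 5.0% | 5.0% | 7.8% | 13.7% |

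A run with skewed outcomes (log-normal, correlation 0.7, 4,000 trials) gave 5.0% for the gated test, 7.0% for the better of the two at one visit, and 12.8% for any of four visits.

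**3. Reading the table.**
- The gate alone does not inflate the error.
- Leaving the gated test and the ANCOVA unranked costs about 1 to 3 percentage points (6–8%).
- Leaving the visit open would cost far more (about 12–16% for one test), but only if success at any visit were accepted. For comparison, four independent tests would give 1 − 0.95⁴ = 18.5%.

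**The case against.** **The ANCOVA is plainly primary.** The Statistics section attaches it to the primary outcome, so the t or Wilcoxon test could be read as the general method for everything else. This is a fair reading, but the text does not settle it. The group-comparison sentence is not limited to other outcomes, the covariates are first called only possible, and the sample size is that of the unadjusted test.

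**Follow-up 1 is plainly the primary visit.** The later DASH assessments are assigned to sustainability, the Abstract calls them long-term results, and the sample size spends all of alpha once. This largely stands. A reader might infer that the plan allows success at any of four visits. The documents do not say so, and the 12–16% is a worst case. What remains is that the visit is implied and never named.

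**The gate is harmless.** For type I error, yes. The article also does not say whether normality is checked overall or by arm, and a check by arm is close to checking t-test residuals. The change of estimand remains.

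**Visit window.** A reader might infer from the 3–5 week range that robot patients who finish late are assessed later in natural recovery than controls. The documents do not support this. Follow-up 1 comes after the last potential training session for all participants, both arms have a 3-week therapy period, and nothing extends the robot course until every session is done. No between-arm lag is described, so no bias is claimed here.

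**Conclusion.** The point holds as a badly fixed analysis rule of moderate weight. The article plans two unranked analyses of the primary DASH outcome, lets a normality test choose the form of one of them, and leaves the primary visit to inference.

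The supported size is a type I error of about 6–8% instead of 5% at one visit, if either analysis may count. This assumes that severity explains 0–30% of DASH variance and that therapy units are unrelated to arm. The larger 12–16% (correlation 0.5–0.8) describes a freedom that the article leaves open by not naming a visit. It is not a decision rule that the article states.

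**What to change.** Before any unblinded comparison, state in the protocol or SAP:

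> The single primary analysis is an ANCOVA of DASH at follow-up 1 with treatment arm, baseline DASH, centre and injury severity. Two-sided alpha 0.05 applies to the treatment-arm contrast only.

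- **List the covariates.** Adopting the ANCOVA as now written would keep number of therapy units in the primary model. That number arises after randomisation. If it includes robot sessions, it is tied to arm. If it does not, the Limitations section itself allows that robot training may change participation in other exercise. Adjusting for it could remove or distort part of the treatment effect. Use it descriptively or in a labelled exploratory analysis.
- **Include baseline DASH.** The article's covariate list omits it. With it in the model, the arm effect is the same whether final value or change is analysed, which closes that gap too.
- **Drop the Shapiro-Wilk gate.** Inspect the model residuals, and give a rank-based or permutation analysis as sensitivity whatever they show.
- **Label the rest.** The unadjusted group comparison becomes sensitivity, and DASH at 3, 6 and 12 months becomes secondary.

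Cost: wording and slightly more analysis work. The 26 per group and total of 60 need not change on this account, and no visit moves. The article reports recruitment at 50%, so at that stage the change could still be made prospectively.

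### The primary ANCOVA names its covariates but omits baseline DASH, which every participant provides before randomisation; this loses precision without biasing the estimate

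*Protocol article*

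**What the plan says.** The abstract names the outcome: "The primary outcome parameter will be the DASH". The Primary outcome section describes the endpoint as a score ("The endpoint will be a score calculated from the ratings of the individual responses") and does not call it a change from baseline.

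DASH is one of the baseline measures listed in the abstract, in the sentence that begins "The baseline assessment will include cognition"; the abstract also places this assessment before randomisation. The Clinical assessment section confirms that it covers everyone: "The clinical assessment will be carried out for all participants before the first potential training session (baseline").

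The Statistics section then specifies the primary model, in the sentence that begins "For the primary outcome analysis of covariance with study centre, number of therapy units" and goes on to add injury severity as the third and last covariate. An earlier sentence there mentions only centre and number of treatment units as possible covariates. Baseline DASH is in neither list. The only other group comparison named, a t test or Wilcoxon test, is unadjusted.

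**The concern.** The pre-treatment value of an outcome is commonly among the best predictors of its later value. Here it costs nothing to use, because it is already collected. The covariates are listed by name, with reasons for two of them, so this is a stated choice and not a detail left to an analysis plan.

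Baseline function is likely to vary widely. "Participants will be included between the fourth and seventh weeks after surgery", and the pilot baseline SD was 20 DASH points. The design does not balance it: randomisation is blocked within centre, and stratification is by fracture location and handedness.

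What is at stake is precision. With about 26 analysed patients per arm, the residual variance is larger than it needs to be, and part of any chance difference in baseline DASH carries into the follow-up comparison.

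**Working it through.** **Inputs.** From the Sample size section: pilot DASH mean 46 (SD 20) falling to 32 (SD 15), 26 per group, 80% power, α = 0.05. The baseline/follow-up correlation r is in no part of the protocol; 0.3, 0.5 and 0.7 are assumed.

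**1. The planned sample size.** Difference = 46 − 32 = 14. SD = √((20² + 15²)/2) = 17.68. Standardised difference = 14/17.68 = 0.792. The two-sided normal formula n = 2 × [17.68 × (1.960 + 0.842)/14]² gives 25.03, rounded up to 26 per group. The exact t test gives 26.02, with power 79.96% at 26. The stated figure therefore reproduces as an unadjusted two-group comparison, so the sample size takes no credit for baseline adjustment.

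**2. Gain in precision.** Adding baseline DASH multiplies the residual variance by 1 − r² and the standard error by √(1 − r²), compared with no covariates. The equivalent n per group is 26/(1 − r²). Power is from the two-sided t test at 26 per group with SD 17.68 × √(1 − r²), ignoring the one degree of freedom used.

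| r (assumed) | 1 − r² | SE ratio | Equivalent n per group | Power at 14 points (planned) | Power at 10 points (assumed) |
|---|---|---|---|---|---|
| no covariate | 1 | 1 | 26 | 80% | 52% |
| 0.3 | 0.91 | 0.954 | 29 | 84% | 55% |
| 0.5 | 0.75 | 0.866 | 35 | 90% | 64% |
| 0.7 | 0.51 | 0.714 | 51 | 97.5% | 80% |

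The 10-point difference is not in the protocol. It shows the gain if the true effect is smaller than planned.

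**3. Sensitivity to the SD.** A comparison of follow-up scores would use the follow-up SD. With SD 15, power at 10 points is 65% without a covariate and 70%, 78% or 91% with baseline DASH at r = 0.3, 0.5 or 0.7. Power is higher throughout and the gain remains.

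**4. Chance imbalance.** The SE of the baseline difference is 20 × √(2/26) = 5.5 points. The chance of an imbalance above 5 points in either direction is 2 × [1 − Φ(5/5.547)] = 37%. In an unadjusted follow-up comparison, imbalance carries through at the slope r × 15/20:

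- r = 0.3: slope 0.225, so 5 points at baseline shift the comparison by 1.1 points
- r = 0.5: slope 0.375, shift 1.9 points
- r = 0.7: slope 0.525, shift 2.6 points

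The planned effect is 14 points.

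**The case against.** **Randomisation already protects the estimate.** This stands. A reader might infer that a baseline difference passes in full into the treatment effect, or that the planned result would be biased. Neither follows. Only the slope-weighted part carries through, and over repeated randomisations the unadjusted estimate is unbiased. The 5.5-point SE is that of the baseline difference, not an error in the treatment effect.

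**The comparison in the table is not with the written plan.** This also stands. The factor 1 − r² is measured against no covariates, whereas the plan already adjusts for centre and injury severity. Where these share information with baseline DASH, the added gain is smaller, and it depends on the partial correlation. The equivalent of 51 per group should not be read as the gain over the planned ANCOVA.

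**The trial has its 80% power without adjustment.** True at 14 points. A reader might take 52% as the trial's real power, but that figure rests on an assumed smaller effect and on SD 17.68. It illustrates the gain and does not show that the trial is underpowered.

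**The correlation may be low.** At r = 0.3 the variance falls by only 9% and power at 10 points moves from 52% to 55%. The protocol does not exclude that value. The gain would then be small, but so is the cost.

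**The endpoint may be meant as change from baseline.** The protocol does not say so. Change would address imbalance in part, but less efficiently: with the pilot SDs and r = 0.5, the SD of change is √(400 + 225 − 2 × 0.5 × 20 × 15) = 18.0, against a baseline-adjusted residual SD of 15 × √0.75 = 13.0.

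**Conclusion.** The point holds as a recommendation on precision. The primary model omits a pre-randomisation covariate that is measured in every participant and is likely to be prognostic. The omission is certain from the text; the size of the loss is not, because r is assumed. For r from 0.3 to 0.7 the standard error would be about 5% to 29% smaller than with no covariates, and possibly less than that relative to the planned ANCOVA. Chance imbalance is only partly addressed, through whatever centre and injury severity share with baseline DASH. The trial is not invalid without the change, but the change should be made.

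**What to change.** Add baseline DASH as a prespecified covariate in the primary ANCOVA of follow-up DASH, and report the adjusted mean difference between arms with its 95% CI. State this before the data are analysed; the Trial status section puts recruitment at 50% when the article was published.

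The cost is a change of wording and one degree of freedom. No new data, visits or patients are needed, and the sample size can stay as it is. Whether the number of therapy units belongs in the model, and which follow-up is the primary time point, are separate questions that this change does not settle.

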### Limitations

The sample size is relatively small and powered only for a functional endpoint (DASH). Social or economic endpoints such as return to work or cost-effectiveness of this intervention would require larger sample sizes and were not the purpose of this early-stage RCT. Furthermore, the set-up with three different associated centres will lead to some difficulties in the standardisation of the assessments. It is expected that different observers and therapists in the three institutions have subjective differences in the accomplishment of the tests. Assessment of the WMFT will be videotaped to standardise this as much as possible.

Heterogeneous treatment modalities will also exist to some extent for rehabilitation after PHF in the conventional occupational and physical therapy in terms of duration, intensity and frequency. Theoretically, participation in the robotic group could lead to increased or decreased motivation to participate in other types of exercises. Adherence will therefore be documented.

For dissemination the full and optimised training protocol will be provided via an online research platform. Also two videos, one about the instructions of the WMFT-O and one about the rating, are provided on YouTube (https://www.youtube.com/watch?v=8yDcWK9Xrtw, https://www.youtube.com/watch?v=MsfrGauYHfc).

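### The primary ANCOVA adjusts for therapy units accrued after randomisation, so its arm coefficient may not estimate the effect of adding robot training

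*Protocol article*

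**What the plan says.** The Statistics section of the protocol article mentions the covariate twice. It opens with "The centre and the number of treatment units will be regarded as possible covariates for the primary outcome". Later it states, without the qualifier, that an ANCOVA will be performed for the primary outcome with study centre, "number of therapy units (to take account of the training inhomogeneity") and injury severity as covariates. The same paragraph plans a group comparison by t test or Wilcoxon test and declares an intention-to-treat approach for inference.

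The article does not say which sessions count as therapy units. Three other places bear on this:

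- **Intervention, robot arm:** the robot arm receives "supervised exercise four times per week for 30 minutes per session" for three weeks. This section also calls a robot session a therapy unit when it describes how the exoskeleton is adjusted beforehand.
- **Intervention, conventional care:** conventional therapy is typically given three to six times a week in both arms. It is recorded but not controlled.
- **Limitations:** the article allows that, in theory, "participation in the robotic group could lead to increased or decreased motivation to participate in other types of exercises".

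**The concern.** Centre and injury severity are fixed before randomisation; the number of therapy units received is not. A covariate that allocation can change should not be in the model that estimates the effect of allocation. The coefficient then compares arms at an equal number of units, whereas the trial asks what happens when robot training is added to usual therapy.

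Two things are at stake. If the covariate largely repeats the arm indicator, the standard error grows and a real effect can be missed. If units lie on the path from allocation to DASH, or share causes with DASH, the coefficient can be biased in either direction.

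**Working it through.** **Planned figure.** The Sample size section gives "median 47 [mean 46 ± 20 SD] to median 34 [mean 32 ± 15 SD" from the pilot and concludes that "26 patients per group will be required to achieve 80% power at a significance level of α = 0.05". The difference is 46 − 32 = 14 and the pooled SD is √((20² + 15²)/2) = 17.68, so d = 0.79. A two-sided 5% test with 80% power needs 26 per group, as stated (t-based solution 26.02). Sidedness and pooling are inferred, because they reproduce the stated number; a one-sided test would need 20. At 26 per group, power is 0.80 (t-based) or 0.81 (normal approximation). The 14 points are used here only as the planned effect.

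**Method.** With arm and units in the model, VIF = 1/(1 − R²), where R² is the squared correlation between arm and units. The SE is multiplied by √VIF. Power ≈ Φ(14/(17.68 × √(2/26) × √VIF) − 1.96) = Φ(2.855/√VIF − 1.96). The results were checked by simulating 4,000 trials per scenario with 26 per arm.

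**Reading A: robot plus conventional sessions.**

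- Robot sessions: 4 × 3 = 12 in one arm, 0 in the other. With 1:1 allocation, the between-arm variance is (12/2)² = 36.
- Conventional sessions: 3 to 6 a week × 3 weeks = 9 to 18. The article gives no spread. A uniform spread (assumption) has variance 9²/12 = 6.75, SD 2.6.

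| Within-arm SD (assumed) | R² | VIF | SE multiplier | Power |
|---|---|---|---|---|
| 2.6 | 36/42.75 = 0.84 | 6.33 | 2.52 | 0.20 |
| 4 | 36/52 = 0.69 | 3.25 | 1.80 | 0.35 |
| 6 | 36/72 = 0.50 | 2.00 | 1.41 | 0.52 |

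The simulated power at SD 2.6 is 0.19, against 0.80 without the covariate. Restoring 80% at that spread would take about 159 per arm. An SD of 6 is a generous upper case: values confined to 9-18 cannot have an SD above half the range, 4.5.

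The estimate can also move. If the whole 14-point benefit works through the 12 extra sessions (14/12 = 1.17 points each), the expected adjusted arm effect is 14 − 12 × 1.17 ≈ 0 (simulated power 5%). If half does, it is about 7 points (simulated power 9%).

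**Reading B: robot sessions only.** The covariate is about 12 against 0. With an attendance SD of 1 to 3 in the robot arm and 0 in control (assumption), the average within-arm variance is 0.5 to 4.5. The VIF is 36.5/0.5 = 73 to 40.5/4.5 = 9, and power is 5% to 16%.

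**Reading C: conventional sessions only.**

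- *Allocation does not shift attendance:* VIF = 1, simulated power 0.79, no bias.
- *Allocation shifts attendance by 2 sessions (assumption):* R² = 1/(1 + 6.75) = 0.129, VIF 1.15, power 0.76 by formula and 0.74 simulated.
- *Bias with that shift, sessions help:* if the robot arm attends 2 fewer and each session lowers DASH by 1 point (assumption), the adjusted benefit is overstated by 2 × 1 = 2 points.
- *Bias with that shift, shared cause:* suppose instead that attendance and DASH share an unmeasured cause with loading 0.5 each (assumption). The slope of DASH on units is (0.5 × 2.6 × 0.5 × 17.68)/(6.75 + 1.3²) = 11.5/8.44 ≈ 1.36, and 2 × 1.36 = 2.7 points. The simulation also gives 2.7, with 7.8% rejection under the null instead of 5%.

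The same shared cause under reading A gives 12 × 1.36 ≈ 16 points for a treatment with no effect (simulated 16.0, rejection 29%). The sign depends on whether patients who do worse attend more or less.

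**The case against.** The strongest reply is that the covariate probably means conventional sessions. Its stated purpose is to handle training inhomogeneity. The Limitations section places heterogeneity in conventional care, and the adherence paragraph under Clinical assessment records the duration and frequency of conventional therapy. Robot training is described as standardised. This stands as a plausible reading, but it does not settle the matter, because the Intervention section uses the same term for a robot session.

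The article also calls units only possible covariates in one sentence and plans a t test or Wilcoxon comparison, which does not condition on units. Both soften the problem. Neither cures it, because the later sentence ties the ANCOVA to the primary outcome and says that it will be done.

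A reader might infer three stronger claims, which the document does not support:

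- **Precision is lost on any reading.** It is not: if only conventional sessions count, the loss is small.
- **Conventional attendance is a mediator.** The Limitations sentence raises a theoretical change in motivation. It does not report an effect on sessions.
- **The model contradicts the intention-to-treat statement.** That statement concerns analysing all randomised patients, with imputation where data are incomplete. The covariate undermines what the estimate means, but the two sentences can both be carried out.

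**Conclusion.** The point holds. The article fixes an undefined post-randomisation covariate in the ANCOVA for its primary outcome. Allocation changes this covariate by design if robot sessions count, and may change it otherwise. The size of the problem depends on the definition:

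- **Robot sessions added to conventional ones:** ANCOVA power of about 20-52% instead of 80%, and loss of any benefit that works through the extra sessions.
- **Conventional sessions only:** power of about 0.74-0.79, and a bias of about 2 to 3 points only if allocation changes attendance.

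The within-arm spreads, the 2-session shift, the 1-point slope and the shared-cause loading are assumptions; the document gives none of them. The 12 robot sessions, the 9-18 conventional units and the 14-point effect come from the article. The power figures apply to the ANCOVA, not to the t test or Wilcoxon comparison. No reading gives a reason to keep the covariate in the primary model.

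**What to change.** In the Statistics section, delete therapy units from the primary ANCOVA and from the sentence on possible covariates. Adjust the primary model only for variables fixed before randomisation: centre and injury severity. Baseline DASH is already collected and could be added, but that is a separate, optional gain and is not needed to cure this defect.

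Report conventional and robot units separately by arm, as a description of what was delivered. If a dose-response analysis is wanted, define the units, and label the analysis exploratory and non-randomised.

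The cost is two edited sentences in the protocol and any analysis plan, made before unblinded analysis. Data collection does not change.
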